### 5.1.2 Clinical Procedures

- ⊗ Medical history, including Review of Systems (ROS)\*
  - \* *Note for female participants this includes notation of the Last Menstrual Period (LMP)*
- ⊗ Ascertainment of current medications
- ⊗ Basic physical examination, including but not limited to the following systems:
  - Cardiovascular
  - Respiratory
  - Gastrointestinal, including anoscopy
  - Any system indicated by a positive medical history or ROS
- ⊗ Collect blood and rectal swab specimens

### 5.1.3 Laboratory Procedures

- ⊗ Safety labs (~10ml of blood)
  - Complete blood count
  - Complete metabolic panel, including magnesium
  - If female of child-bearing potential, Qualitative HCG

- ⊙ STD Screen (for potential rectal infections only)
  - (~10ml of blood)
  - HIV-1 serology (See Appendix IV for testing algorithm)
  - RPR or VDRL
  - (3 anorectal swabs)
  - Rectal HSV by culture
  - Rectal *Chlamydia trachomatis* by culture
  - Rectal *Neisseria gonorrhea* by culture

## 5.2 Visit 2- Enrollment (Week 0)

### 5.2.1 Non-clinical Procedures

- ⊙ Update locator information and remind participant that he or she will receive visit reminders via email and/or telephone.
- ⊙ Provide test results from screening visit and post-test counseling.  
*If any lab abnormalities ≥Grade 2, subject may not proceed with Visit 2. If the investigator feels that the laboratory abnormalities are transient, the lab tests may be repeated within the visit window. If the repeated labs tests are within normal limits, the subject may proceed with Visit 2 at the discretion of the investigator, the DAIDS Medical Officer, the SMC, and the IRB.*
- ⊙ If subject had a positive STI result at Visit 1, the subject will be referred for treatment of that STI. The subject may proceed to enrollment (Visit 2) one week after a CDC-approved (Appendix X) treatment for the STI.
- ⊙ Collect copy of concomitant medication log
- ⊙ Review precautions listed in Section 5.1.1.
- ⊙ Instruct subject in use of CASI for Baseline Behavioral Questionnaire (BBQ).

Eligible participants who are computer literate will be able to respond to the survey either from their homes or using a terminal at one of the researchers' offices.

Participants who are not computer literate will be given a short tutorial on using the computer to answer questions. When the participant feels comfortable, the research assistant will start the CASI program for the participant. The research assistant will remain in the room while the participant answers the questions but will sit so that he does not see the answers being entered. The research assistant will help with computer questions or problems. If a respondent does not understand a question, the research assistant will read the question aloud, referring to a paper copy of the interview and identifying the question by its number.

### 5.2.2 Clinical Procedures

- ⊙ Interval medical history\*, including AE assessment, will be collected to assure continued healthy status and safety of study interventions.  
*\* Note for female participants this includes notation of the LMP.*
- ⊙ Basic physical examination as defined in section 5.1.2  
*(If participant has peri-anal or rectal HSV lesions, referrals for treatment will be provided and Visit 2 will be postponed until outbreak resolved.)*
- ⊙ Collect blood and rectal swab specimens
- ⊙ Collect rectal sponge specimens
- ⊙ Administer preparatory Normosol-R pH7.4 enema
- ⊙ Collect stool specimen

- ⊙ Perform flexible sigmoidoscopy, including:
  - Rectal lavage at approximately 5cm
  - 14 biopsies at approximately 10cm
  - 14 biopsies at approximately 30cm
  - \* *each biopsy measures 8 mm x 2 mm x 1 mm*

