Rationale: The gastrointestinal mucosa secretes protective mucosal antibodies (mainly IgA and IgG) continuously which, coupled with the physical barrier effects of mucosal mucus, enhance protection. Selective amplification of HIV-specific antibodies has been the goal of most HIV vaccine trials, including the few that have begun to investigate mucosal specific forms. In microbicide trials, changes from baseline levels of total mucosal Ig (or IgA/IgG subsets) may be used to evaluate potential hypersensitivity or immune compromise induced by the study products. Mucosal secretions will be collected using surgical sponges applied topically. These secretions will then be analyzed for IgA/IgG titers.

- Fecal calprotectin

Rationale: Calprotectin accounts for 60% of the cytoplasmic protein fraction of polymorphonuclear granulocytes and is also found in monocytes, macrophages, and eosinophils. Calprotectin plays an important role in innate immunity and has antibacterial, antifungal, and immunomodulatory effects in vivo.

Because intestinal granulocytes end their lifespan by migration through the intestinal wall and granulocyte-derived calprotectin can be found in feces, calprotectin is felt to be a useful indirect index of mucosal inflammation. In fact, fecal calprotectin levels are elevated in inflammatory bowel disease and correlate well with disease activity in Crohn's disease and ulcerative colitis. In addition, fecal calprotectin levels have been found to be significantly elevated in first-degree relatives of patients with Crohn's disease even though all the relatives were clinically asymptomatic. These data suggest that the fecal calprotectin assay may be sufficiently sensitive to respond to subtle increases in mucosal inflammation. Fecal calprotectin has a sensitivity of 96% in discriminating between healthy controls (2mg/l; 95% CI 2-3 mg/l) and subjects with active inflammatory bowel disease (91 mg/l; 95% CI 59-105 mg/l). Stool samples will be collected at the time of rectal lavage for the measurement of fecal calprotectin.

- Explants- Mucosal cytokines and susceptibility to HIV infection

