### 5.3.2 Clinical Procedures

**NOTE: During this visit the timepoints listed below are approximate. Every effort will be made to adhere to the timeline, however due to logistics timing will not be exact. However, the sequence of sample collection during the following visits is crucial.**

- ⊙ Interval medical history\*, including AE assessment, will be collected to assure continued healthy status and safety of study interventions.
 

*\* Note for female participants this includes notation of the LMP.*
- ⊙ Basic physical examination as defined in section 5.1.2
 

*(If participant has peri-anal or rectal HSV lesions, referrals for treatment will be provided and Visit 3 will be postponed until outbreak resolved.)*
- ⊙ **If female of child-bearing potential, collect urine for STAT HCG testing**
- ⊙ Collect blood specimens, including pre-dose pK draw if applicable
- ⊙ Collect rectal swabs and sponge specimens

- ⊙ Administer preparatory Normosol-R pH7.4 enema
- ⊙ Collect stool specimen
- ⊙ T=0 Administration of single-dose of study gel by study staff  

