The cytokine data in HPTN 056 and earlier work of our group for RANTES, IFN- $\gamma$ , and IL-10 all showed strong stability (intrasubject correlations between 0.7 or 0.8; analysis is on log-transformed scale for all three of these). Again, this suggests that any clinically meaningful differences between treatment groups are likely to result in small p-values.

- Mucosal immunoglobulins

The immunoglobulin data collected in HPTN 056 appears to be moderately stable within subject (intrasubject correlations are between 0.3 and 0.5 for various measures of IgA and IgG).

- Fecal calprotectin

The fecal calprotectin marker has been shown to be extremely sensitive for discriminating several clinical conditions such as active and inactive Crohn's disease. The large majority of measurements for inactive subjects were below normal thresholds and nearly all measurements for active subjects were above normal thresholds. For our study, this suggests that this marker will be particularly helpful in detecting evidence of mucosal damage in the treatment groups.

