#### **RISKS FROM ENEMAS**

The main risk from having an enema is temporary discomfort. A hollow tube about the thickness of a pencil will be used to put approximately 125ml of Normosol-R pH7.4 into the

rectum and flush it out again (a larger volume may be required if the initial volume does not produce results), along with any stool that is there. This may cause a “bloated” or “crampy” feeling. Some air may be pumped into the rectum as well, causing flatulence. The tube is small, but it might cause some anal or rectal discomfort if the subject has any hemorrhoids or other painful conditions. The impact of the rectal application of UC-781 on the intestinal mucosa is unknown and may increase the risk of discomfort.

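### Stool for fecal calprotectin is collected after an enema of variable volume with no stated control for dilution, and the sections disagree on whether the Visit 3 stool is pre- or post-dose

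*Protocol*

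**What the plan says.** **Collection order.** Sections 5.2.2 (Visit 2), 5.3.2 (Visit 3) and 5.7.2 (Visit 5) each list "Administer preparatory Normosol-R pH7.4 enema" and, directly after it, "Collect stool specimen". Rectal sponges are listed before the enema at all three visits, with a second set after dosing at Visit 3. Section 5.3.2 says that timepoints are approximate but that "the sequence of sample collection during the following visits is crucial", so the listed order is meant to be followed.

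**Volume.** Section 8.3 (risks from enemas) says that a tube is used to "put approximately 125ml of Normosol-R pH7.4 into the" rectum, and that "a larger volume may be required if the initial volume does not produce results". No upper limit is given.

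**Role of the marker.** Fecal calprotectin is a secondary parameter of mucosal damage. Section 2.1.2 says that "the fecal calprotectin assay may be sufficiently sensitive to respond to subtle increases in mucosal inflammation". It cites a 96% sensitivity for separating healthy controls (2 mg/l) from active inflammatory bowel disease (91 mg/l). Section 7.6 expects that "this marker will be particularly helpful in detecting evidence of mucosal damage in the treatment groups". It analyses the marker by ANCOVA on the baseline value, and also without baseline.

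**Visit 3 timing.** In Section 5.3.2 the stool step comes before "T=0 Administration of single-dose of study gel by study staff". The Schema lists stool among the specimens obtained within about 30 minutes after the dose. Section 2.1.2 places stool at the time of rectal lavage. Section 7.6 counts calprotectin as measured at baseline, post-Treatment 1 and post-Treatment 2.

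**The concern.** Stool passed after an enema may carry some of the enema fluid. If it does, a concentration measured in it falls by a factor that depends on the amount of stool, the volume given and the degree of mixing. None of these is recorded or corrected for in the Protocol, and each can differ between a person's baseline and post-treatment visits.

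Two things are at stake. The first is precision. Dilution noise in both the baseline and the outcome lowers their correlation, and the ANCOVA depends on that correlation. Section 7.6 quotes intrasubject correlations for phenotype, cytokines and immunoglobulins but none for calprotectin, so its stability is unsupported even before dilution. The second is level. Section 7.6 supports the marker by where values fall relative to normal thresholds. Dilution moves every value towards normal, and equal handling of the arms does not remove that error.

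Elsewhere the Protocol treats bowel preparation as a possible confounder: Section 2.1.2 replaces the standard hypertonic enema for that reason. It gives no reason for not taking stool, like the sponges, before the enema.

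**Working it through.** The Protocol gives no SD, power or detectable difference for calprotectin, so there is no figure of its own to reproduce.

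**Inputs from the Protocol:** nominal volume 125 ml, possibly more (Section 8.3); 12 per arm (Schema); cited values of 2 and 91 mg/l (Section 2.1.2).

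**Assumptions, not in the Protocol:** stool mass 50 to 300 g; increased volume 250 ml, with 500 ml as an outer case; all fluid retained and fully mixed; log-scale SD 0.5 to 1.0.

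**1. Dilution factor** = (stool + enema) / stool, taking 1 g as 1 ml.

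| Stool | 125 ml | 250 ml | Ratio 250/125 |
|---|---|---|---|
| 50 g | 175/50 = 3.50 | 300/50 = 6.00 | 1.71 |
| 100 g | 225/100 = 2.25 | 350/100 = 3.50 | 1.56 |
| 200 g | 325/200 = 1.63 | 450/200 = 2.25 | 1.38 |
| 300 g | 425/300 = 1.42 | 550/300 = 1.83 | 1.29 |

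Raising the volume from 125 to 250 ml therefore changes a result 1.29- to 1.71-fold. Raising it to 500 ml changes it 1.88-fold (300 g) to 3.14-fold (50 g). With the volume held at 125 ml, stool mass alone gives up to 3.50/1.42 = 2.5-fold.

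**2. Comparison with the signal.** The cited disease contrast is 91/2 = 45.5-fold, far larger than any of these factors. A subtle rise of 1.5- to 2-fold is about the same size as the artefact within one person.

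**3. Effect on the comparison between arms.** Take stool mass as uniform on 50 to 300 g and volume as 125, 250 or 375 ml with probabilities 0.7, 0.2 and 0.1. The log dilution factor then has SD 0.34. Adding this in quadrature to the assumed log-SD s gives a total SD of √(s² + 0.34²). For 12 per arm, two-sided 0.05 and no baseline adjustment, the fold difference detectable with 80% power is exp[(1.96 + 0.84) × SD × √(2/12)].

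| Assumed log-SD | Detectable fold, no dilution noise | With it | Power for 2-fold, without | With |
|---|---|---|---|---|
| 0.5 | 1.77 | 2.00 | 0.92 | 0.80 |
| 0.8 | 2.50 | 2.70 | 0.56 | 0.50 |
| 1.0 | 3.14 | 3.35 | 0.40 | 0.36 |

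**4. Effect on the baseline covariate.** If dilution noise is independent between visits, the baseline-to-outcome correlation is multiplied by s²/(s² + 0.34²). At s = 0.5 this is 0.25/0.3656 = 0.68, at s = 0.8 it is 0.64/0.7556 = 0.85, and at s = 1.0 it is 1/1.1156 = 0.90.

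**5. Visit 3, sections side by side.** Section 5.3.2 runs enema, stool, gel at T=0, then lavage at about 30 minutes. A specimen taken at that step cannot carry an effect of the gel. The Schema and Section 7.6 treat it as post-dose, and Section 2.1.2 ties it to lavage, which Section 5.3.2 places after dosing. These cannot all describe the same specimen.

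**The case against.** The strongest case on the other side has five parts.

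- **The arms are handled alike.** Enema and stool steps are identical in all arms, and the main question is a randomised comparison with placebo. Dilution then costs precision and lowers levels. Bias between arms would need the gel to alter stool or the need for more enema fluid by Visit 5, and nothing in the Protocol suggests that. This stands.
- **Mixing is assumed.** The Protocol names a stool specimen separately from the lavage fluid and does not say that effluent is assayed. Formed stool would be less affected. This stands, and makes the factors above upper bounds for the stated masses and volumes.
- **Handling may be settled elsewhere.** The mg/l values belong to a cited study. The Protocol does not state this trial's reporting unit, and it leaves detailed procedures to a manual that is not shown. Normalisation may be specified there. The order of collection, however, is fixed in the Protocol.
- **Sample size is the larger limit.** At log-SD 0.8 or 1.0, dilution costs 4 to 6 points of power from an already low level. Even a 6-fold dilution leaves the cited 91 mg/l at about 15 mg/l (91/6), well above 2. So a gross rise would still show.
- **The claims are hedged.** Section 2.1.2 says only that the assay may be sensitive enough, and also points to raised levels in symptom-free relatives of Crohn's patients. Section 1.1 says that these developing assays are not safety indices. This limits the consequences. It does not make the 96% figure, which comes from active disease, evidence about small changes.

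**Conclusion.** The point holds as a weakness in measurement that is cheap to improve. The order of enema before stool, the open-ended volume and the absence of any stated control for dilution are all in the text. Under the assumed 50 to 300 g and full mixing, a change from 125 to 250 ml shifts a value about 1.3- to 1.7-fold. The result is added noise, a weaker baseline covariate and readings biased low against normal thresholds.

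A reader might infer more: that dilution differs at every visit and that subtle inflammation therefore cannot be measured. The Protocol does not support this. The larger volume is conditional, the degree of mixing is unknown, and the between-arm comparison loses some power but is not invalidated. Nor does Section 7.6 promise detection of subtle damage. It speaks of mucosal damage in general, and the word subtle occurs only in the hedged sentence in Section 2.1.2.

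The Visit 3 contradiction is separate and rests on no assumption. Until it is settled, the Visit 3 calprotectin value should not be analysed as post-treatment.

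**What to change.** 1. At Visits 2 and 5, collect the calprotectin stool before the enema, by the same method at both visits (brought from home or passed on arrival).
2. Where that is not possible, record the enema volume and report calprotectin per gram of dry weight. Agree this with the laboratory that runs the assay; Sections 9.1 and 9.2 list it under both the local research laboratory and an outside one.
3. Qualify the sentence in Section 7.6 on the marker's usefulness. The 96% sensitivity in Section 2.1.2 is for active bowel disease against healthy controls and does not establish sensitivity to small changes.
4. Reconcile the Visit 3 stool timing across the Schema and Sections 2.1.2, 5.3.2 and 7.6. Do not extend item 1 to Visit 3 before this is done: the enema precedes dosing there, so a pre-enema sample would be pre-dose by construction. If a post-dose sample is intended, it will follow the enema. Its absolute change from a pre-enema baseline would then not be interpretable, although the comparison between arms would be.

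The cost is a collection kit, a reordered procedure list and some missing samples when no stool is produced in time.

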### 5.2.3 Laboratory Procedures

- ⊙ Safety labs as defined in section 5.1.3
- ⊙ STD screen as defined in section 5.1.3
- ⊙ Research panel
  - Epithelial sloughing assay (Lavage)
  - Histopathology (~1 biopsy)
  - Microflora (~1 rectal swab)
  - Mucosal mononuclear cell phenotype (~4 biopsies)
  - Mucosal cytokine profile (~3 biopsies)
  - Immunoglobulin assay (~2 rectal sponges)
  - Fecal calprotectin assay (Stool)
  - Explants studies (~6 biopsies, ~10ml blood)

## 5.3 Visit 3- (Week 2 +/- 1 week) Single Dose Administration

### 5.3.1 Non-clinical Procedures

- ⊙ Randomize subject and assign participant ID number prior to Visit Day
- ⊙ Provide test results from Visit 2 and post-test counseling.
 

*If any lab abnormalities ≥Grade 2, subject may not proceed with Visit 3. If the investigator feels that the laboratory abnormalities are transient, the lab tests may be repeated within the visit window. If the repeated labs tests are within normal limits, the subject may proceed with Visit 3 at the discretion of the investigator, the DAIDS Medical Officer, the SMC, and the IRB.*
- ⊙ If subject had a positive STI result at Visit 2, the subject will be referred for treatment of that STI. The subject may proceed to Treatment Stage 1 (Visit 3) one week after a CDC-approved (Appendix X) treatment for the STI.
- ⊙ Update locator information and remind participant that he or she will receive visit reminders via email and/or telephone.
- ⊙ Collect copy of concomitant medication log
- ⊙ Review precautions listed in Section 5.1.1.

### 5.3.2 Clinical Procedures

**NOTE: During this visit the timepoints listed below are approximate. Every effort will be made to adhere to the timeline, however due to logistics timing will not be exact. However, the sequence of sample collection during the following visits is crucial.**

- ⊙ Interval medical history\*, including AE assessment, will be collected to assure continued healthy status and safety of study interventions.
 

*\* Note for female participants this includes notation of the LMP.*
- ⊙ Basic physical examination as defined in section 5.1.2
 

*(If participant has peri-anal or rectal HSV lesions, referrals for treatment will be provided and Visit 3 will be postponed until outbreak resolved.)*
- ⊙ **If female of child-bearing potential, collect urine for STAT HCG testing**
- ⊙ Collect blood specimens, including pre-dose pK draw if applicable
- ⊙ Collect rectal swabs and sponge specimens

- ⊙ Administer preparatory Normosol-R pH7.4 enema
- ⊙ Collect stool specimen
- ⊙ T=0 Administration of single-dose of study gel by study staff  
**If female of child-bearing potential, must confirm HCG negative prior to administration.**
- ⊙ T= 15 min pK draw, if applicable
- ⊙ T= 30 min Collect rectal sponge specimens  
Perform flexible sigmoidoscopy, including:  
Rectal lavage at approximately 5cm  
14 biopsies at approximately 10cm  
14 biopsies at approximately 30cm  
*\* each biopsy measures 8 mm x 2 mm x 1 mm*
- ⊙ T= 2 hr pK draw, if applicable
- ⊙ T= 4 hr pK draw, if applicable  

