## **7.6 Statistical Procedures for Analysis of Mucosal Damage Parameters**

The associations of six sets of mucosal parameters with the use of study product will be examined as a secondary objective. Four of these parameter sets (Histopathology, Cell Phenotype, Cytokine profile, Fecal Calprotectin) are collected three times per patient: at baseline, post-Treatment 1 and post-Treatment 2. The remaining two sets (Epithelial Sloughing and Immunoglobulins) are four times per patient: at baseline, pre- and post-Treatment 1, and post-Treatment 2. For all six parameter panels, the main question of interest is whether the three treatment groups (placebo, low, and high) have systematically different mucosal damage parameters post-Treatment 1 and post-Treatment 2. In particular, we will be assessing whether either of the UC-781 treatment groups have evidence of more mucosal damage than the placebo group. As described below, at least four of the six parameter sets should be stable and sensitive enough that important clinical differences would be statistically detectable.

As subjects will be randomized to the three treatment groups, systematic baseline differences are not expected; however, due to the relatively small study size, it is quite likely that many parameters will be quite different between treatment groups at baseline. All analyses will therefore be conducted both with and without controlling for baseline measurements. For continuous measures, it is well-known that controlling for baseline differences in regression models is more powerful than analyzing changes from baseline.

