We will also investigate longitudinal (three or four time points) and/or multivariate (simultaneous examination of multiple measures in a set) modeling techniques. The longitudinal analyses will most likely not be additionally informative, as there are only three time points for most of the parameters. Multivariate techniques are expected to result in potentially substantial power increases. Our previous studies with phenotype and cytokine panels have shown strong correlations between measures as well as good stability over time (i.e. high intrasubject correlations) in steady state for many of the measures. In this setting, for example, factors derived using principal components analysis would likely have stronger association with group membership than any one particular measure in the set. An additional strength of the longitudinal and multivariate approaches is that they provide an alternative solution to the multiple testing problem that arises with examining each timepoint and each parameter individually.

- Epithelial Sloughing

The simplest analysis for the epithelial sloughing measurements will look at the presence or absence of sloughing. Additionally, we may employ the five point ordinal scale of, which ranges from 0 (no evidence of sloughing) up to 4 (evidence in all four quadrants). For these data, there is baseline measurement will allow screening out of post-Treatment 1 false positives.

- Histopathology

As in the sloughing data, we will begin by examination of a two point (normal versus abnormal) or three point (normal, slightly abnormal, abnormal) scales. Based on initial analyses of the HPTN 056 histopathology panel data, we do not expect that quantitative measures will be substantially more informative than simple qualitative readings.

- Mucosal mononuclear cell phenotype

Many of the flow cytometry measurements from the HPTN 056 study are quite stable across time. Parameters with high intrasubject correlations (RFI measures are log-transformed) include %CD3, %CD4, %CD8, %CD31, CD38RFI on CD4+, CD38RFI on CD8+, %CD38|CD4, and %CD38|CD8 which have intrasubject correlations of between 0.7 and 0.9. Thus, we expect that clinically important differences in these parameters between treatment groups would be found to be statistically significant in our analyses. CCR5-related parameters had moderate stability (intrasubject correlations of around 0.5).

- Mucosal cytokine Profile

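### The Visit 3 post-dose immunoglobulin sponge alone follows a same-visit enema and fresh gel, so change from baseline within an arm at that point is not like-for-like; the planned arm comparison is largely protected

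*Protocol*

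**What the plan says.** Protocol Section 7.6 gives the sampling frequency: "The remaining two sets (Epithelial Sloughing and Immunoglobulins) are four times per patient", namely baseline, before and after Treatment 1, and after Treatment 2.

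The visit sections fix the order of sampling. At Visit 2 (Section 5.2.2) the step "Collect rectal sponge specimens" comes before the enema, and Section 5.7.2 (Visit 5) uses the same order. At Visit 3 (Section 5.3.2) the sequence is "Collect rectal swabs and sponge specimens", then "Administer preparatory Normosol-R pH7.4 enema", then "T=0 Administration of single-dose of study gel by study staff", and half an hour later "T= 30 min Collect rectal sponge specimens". Section 5.3.2 allows clock times to be approximate but treats the order of collection as essential. Section 5.3.3 pairs the pre-dose and post-dose immunoglobulin assays.

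On interpretation, Section 2.1.2 says that "changes from baseline levels of total mucosal Ig (or IgA/IgG subsets) may be used to evaluate potential hypersensitivity" or immune compromise. Section 7.6 makes the comparison of the three randomized groups the main question. It uses ANCOVA on the baseline value with placebo as reference, and runs the analysis without baseline as well. It also says "We will also investigate longitudinal (three or four time points" for most or some panels respectively), although it expects little extra information from this.

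**The concern.** Stool, lavage and biopsies follow the enema at every visit where they are taken, so for them the preparation is the same each time. Only the sponge changes position. The enema may remove secretion, and the sponge may then take up gel together with whatever has been re-secreted in about 30 minutes.

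The Visit 3 pre-dose sponge does not solve this, because the enema lies between it and the post-dose sponge. Any before-and-after comparison within an arm at Visit 3 therefore mixes three things: the product, the enema, and the presence of gel. A fall could be taken for immune compromise, or a real rise could be masked. The same holds for a within-arm time effect in a four-time-point model.

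**Working it through.** **Step 1: the plan's own count.** Collections are 1 (Visit 2) + 2 (Visit 3) + 1 (Visit 5) = 4, as Section 7.6 states.

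| Collection | After a same-visit enema? | Most recent gel |
|---|---|---|
| Visit 2 | No | None |
| Visit 3 pre-dose | No | None |
| Visit 3 post-dose | Yes, about 125 ml, more if needed (Section 8.3) | About 30 min before, 3.5 ml (Section 4.2) |
| Visit 5 | No | About one day before, +/- 1 day (Section 5.7) |

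So 1 of 4 follows a same-visit enema and fresh gel.

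**Step 2: inputs for the consequence.** From the documents: 12 per arm, three arms, and intrasubject correlation r of 0.3 to 0.5 for IgA and IgG (Section 7.6). Assumed, because the documents are silent: SD of natural-log immunoglobulin = 1; recovery fraction d at the post-dose sponge = 0.75, 0.50 or 0.25, the same in every arm; SD of log recovery between subjects = 0 or 0.5; no drug effect.

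**Step 3: change within one arm.** The expected shift is ln(d): -0.29, -0.69 and -1.39 (in log10: -0.12, -0.30 and -0.60). In 4,000 simulated trials per setting, a paired t-test in one arm was counted when it showed a fall at two-sided 5% (nominal 2.5% in that direction).

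| d (assumed) | False significant fall, one arm | ANCOVA contrast with placebo | ANCOVA type I error |
|---|---|---|---|
| 0.75 | 11-15% | about 0 | 4.4-5.8% |
| 0.50 | 42-59% | about 0 | 4.8-5.2% |
| 0.25 | 93-99% | about 0 | 4.8-5.1% |

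The ranges span both values of r and both values of the recovery SD.

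**Step 4: contrast between arms.** A common ln(d) adds the same constant to every arm and drops out of the treatment coefficient. Across all settings the mean simulated contrast lay between -0.02 and +0.01.

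**Step 5: precision.** With s the SD of log recovery, the difference detectable with 80% power is about (1.96 + 0.84) x sqrt(1 + s^2 - r^2) x sqrt(2/12), in SD units.
- r = 0.3: sqrt(0.91) gives 1.09 for s = 0; sqrt(1.16) gives 1.23 for s = 0.5.
- r = 0.5: sqrt(0.75) gives 0.99 for s = 0; sqrt(1.00) gives 1.14 for s = 0.5.

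If the covariate is the mean of the Visit 2 and Visit 3 pre-dose values (equal correlations assumed), r^2 is replaced by 2r^2/(1 + r). That is 0.138 for r = 0.3 and 0.333 for r = 0.5. With s = 0.5 the detectable difference becomes 1.21 and 1.10, a modest gain at no sampling cost.

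**Step 6: unequal recovery between vehicles.** The UC-781 gels use carbomer and methylcellulose at pH 5.2; the control gel uses hydroxyethyl cellulose at pH 4.4 (Section 4.2). If recovery were 0.75 with one base and 0.50 with the other (purely illustrative), the contrast with placebo would shift by ln(0.75/0.50) = 0.41 SD. The two UC-781 arms share a base and pH, so the contrast between them would not be affected.

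**The case against.** The strongest reply is that Section 7.6 already puts its weight on the right comparison. All arms have the same enema and the same gel volume, the model is ANCOVA against placebo, and the section itself prefers baseline adjustment to change scores. The sentence in Section 2.1.2 is rationale, worded as a possibility rather than as an analysis rule. The longitudinal models are only to be explored, and a time effect shared by all arms would not bias a group-by-time contrast. Section 1.1 says these assays are secondary endpoints and not safety indices. Sponge elution and normalisation may be set out in the study-specific procedures manual, so the protocol's silence on them is not itself a fault.

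Most of this stands. A reader might infer that the sampling order builds a fall into the data that will look like immune suppression, or that it undermines the post-Treatment 1 arm comparison. The documents support neither. They give no figure for wash-out, sponge uptake or re-secretion, and common losses cancel between arms. Nor do they show that the two gel bases differ in recovery; they show only that the bases differ.

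What the reply does not remove is that Section 2.1.2 offers the change-from-baseline reading without excepting the one time point where it is confounded, and that Section 5.3.3 pairs two Visit 3 samples separated by the enema.

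**Conclusion.** The point holds as a limit on interpretation for one secondary marker at one time point. Change within an arm to post-Treatment 1 cannot be attributed to the product. How misleading it would be depends entirely on recovery, which is unknown: in the assumed range the false-fall rate runs from about 11% to 99%, and it stays at the nominal 2.5% if recovery is complete.

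The main planned analysis is unbiased provided that recovery is equal across arms. That is plausible but not assured, given the different vehicles. Uneven recovery between subjects (SD of log recovery 0.5, assumed) would raise the detectable difference by about 0.14-0.15 SD (1.23 - 1.09 and 1.14 - 0.99).

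Visit 2 against Visit 5 is the more comparable pair for change, since both precede the enema. It is not perfectly clean, because Visit 5 follows the last gel dose by about one day.

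**What to change.** 1. In Sections 2.1.2 and 7.6, state that post-Treatment 1 immunoglobulins are interpreted only as contrasts between arms. Within-arm change, including a within-arm time effect in any four-time-point model, is not read as a product effect at that point.
2. In Section 7.6, enter the already collected Visit 3 pre-dose value as the ANCOVA covariate, alone or averaged with Visit 2.
3. Report IgA and IgG also per unit of total protein for all four collections. Sponge weight would not serve, because it includes absorbed gel.
4. Name Visit 2 against Visit 5 as the preferred pair for describing change, with the note on recent gel use.

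The cost is one protein assay on existing eluates and a few sentences. No visit, sample or procedure changes. The drawback is that total protein could itself respond to the product, so both the raw and the protein-adjusted results should be shown. A difference from placebo that is similar in both UC-781 arms and disappears after adjustment would suggest a recovery effect of the vehicle, but would not prove it.
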